### Randomization and blinding

The pregnant women who participated in the original Tehran Thyroid and Pregnancy Study, with a diagnosis of SCH and/or autoimmune thyroid diseases, were randomly allocated into two groups using a computer-generated list in blocks of four. For the purpose of the current study, the trained examiner who assesses the developmental status of children born from those pregnant women using the ASQ are blinded to the previous grouping of participants.

### Statistical analysis

Intention to treat (ITT) analysis will be considered to deal with non-compliance and missing outcomes in our RCT.

Dataset accuracy will be checked using histograms and cross-tabulations to identify any outliers and errors. We will also run “Grubbs” test, an ESD (method extreme studentized deviate), to determine whether any values are significant outliers or implausible values > 4 SD from the mean will be considered as outliers and discarded. Descriptive statistics will be presented as means ± SD for normal, medians and IQR for non-normal variables, and categorical variables presented as percent.

Normality assumption will be checked by Kolmogorov–Smirnov and Shapiro–Wilk test; in case of rejection, the Mann–Whitney non-parametric U test will be applied, otherwise independent Student’s t test will be used to find the differences. For categorical variables, chi-squared test and/or Fisher’s exact test in case of a sparse data problem (cell < 5) will be used. Subgroup analysis for important confounding variables will be run, if needed.

The primary analysis for the study is to assess the effect of treatment on the aspects of psychomotor developmental status. Therefore generalized linear models (GLM) will be conducted modeling the variables and checking the causal relationships between the outcome of interests and other covariates such as treatment. Crude and adjusted models for potentially confounding effects will be fitted.

Interaction effect of treatment and some other covariates will be added to the model and a subgroup analysis will be run to check the effect of treatment on the levels of covariates, variables such as parity, socioeconomic status, type of delivery, lactic status, urinary iodine, and so on.

Since our study follows up the second generation of the ancestors whom intake the intervention, the casual relationships could be assessed via transitional models. There is a series of statistical analyses to estimate these relationships; we use transitional models which applied Markov Chains stochastic process and multistate models.

Statistical analysis will be performed using STATA software (version 10; STATA, Inc., College Station, TX, USA) and the latest version of R CRAN, the “msm” package, to analyze multi-state modelling with R; *p* < 0.05 is considered statistically significant.

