### Neurodevelopmental study of offsprings

Both groups of children (aged three years) born to mothers with SCH and/or autoimmune thyroid disease will be invited to participate. In the present study, parents will complete the Ages and Stages Questionnaire to assess the children’s developmental status. The children of those euthyroid TPOAb^−^ women will also be invited to be participate in this follow-up study and serve as controls (Fig. 1).

Participants will be contacted by phone; the aim and purpose of the present study will be explained in detail. An appointment will be arranged for those participants who wish to complete the development assessment. A trained examiner will explain the instructions for completing the questionnaire. All assessments will be performed by one examiner only to maximize reliability. A randomly selected 5% of the completed assessments will be retested in two weeks and double-scored to ensure the reliability; the scores are calculated and a report is generated for the participants to be taken to their parents. If participants need to be given more information about the results or have any questions, they can contact the examiner directly.

In the present study, the ASQ, a parent-report questionnaire, was chosen because it has been proven to be a valid and/or reliable screening test for Iranian infants and children [26]. The ASQ questionnaire assesses the developmental status of children aged 4–60 months (in 19 age groups) in five developmental domains including communication, gross motor skills, fine motor skills, problem-solving, and social–personal domains. It includes six open-ended questions that assess the parents’ concerns such as visual and auditory problems. Each age-specific domain includes six items, scores are in the range of 0–60 in each subscale, and the total score is in the range of 0–300 [27]. The scoring system is based on a 10–5–0 scoring scale (10 points for every “yes,” 5 points for every “sometimes,” and 0 points for every “not yet” answer to the questions). The sum of scores is then compared with a list of age-specific cut-off points standardized for Iranian children [26, 28].

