### Power calculation and sample size justification

The purpose of this study will be multiple comparisons of five groups: three groups of controls: no intervention TPOAb^+^, no intervention TPOAb^−^, and healthy; as well as two cases: intervention TOPAb^+^ and TPOAb^−^. We will consider five primary outcomes: communication; gross motor skills; fine motor skills; problem-solving; and social–personal aspects.

Post-hoc power calculation was done to detect samples needed. It has been shown that, with power of 80% and type one error of 5%, nearly 2356, 590, 263, 149, 96, 67, 50, 39, and 31 participants are required to find the effect sizes 0.1, 0.2, 0.3, 0.4, 0.5, 0.6, 0.7, 0.8, and 0.9 statistically significant. We will consider q = 15% attrition as well which increases sample size by n* = n/1-q. The following formula for comparison of groups is applied:$$ \boldsymbol{n}\boldsymbol{\ge}\left(\mathbf{1}+\sqrt{\boldsymbol{g}-\mathbf{1}}\right)\frac{{\left({\boldsymbol{z}}_{\mathbf{1}-\frac{\boldsymbol{\alpha}}{\mathbf{2}}}+{\boldsymbol{z}}_{\mathbf{1}-\boldsymbol{\beta}}\right)}^{\mathbf{2}}}{{\boldsymbol{d}}^{\mathbf{2}}}+\frac{{\boldsymbol{z}}_{\mathbf{1}-\frac{\boldsymbol{\alpha}}{\mathbf{2}}}^{\mathbf{2}}\sqrt{\boldsymbol{g}-\mathbf{1}}}{\mathbf{2}+\left(\mathbf{1}+\sqrt{\boldsymbol{g}-\mathbf{1}}\right)} $$

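### The 4-SD discard rule does not exempt the ASQ primary outcomes and requires no evidence of error, so it can delete valid, very low domain scores

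*Protocol article*

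**What the plan says.** All references are to the protocol article.

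The Statistical analysis section opens with "Intention to treat (ITT) analysis will be considered to deal with non-compliance and missing outcomes in our RCT". The next paragraph, on checking the dataset, adds "We will also run “Grubbs” test, an ESD (method extreme studentized deviate), to determine whether any values are significant outliers" and continues that "implausible values > 4 SD from the mean will be considered as outliers and discarded". It names no variable as covered or exempt. It mentions no check against the questionnaire and no analysis with the values kept.

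The Power calculation section names the outcomes: "We will consider five primary outcomes: communication; gross motor skills; fine motor skills; problem-solving; and social–personal aspects". The section on the neurodevelopmental study of offspring gives their scale. There are six items per domain, with "10 points for every “yes,” 5 points for every “sometimes,” and 0 points for every “not yet” answer", and "scores are in the range of 0–60 in each subscale, and the total score is in the range of 0–300". It also says how a score is read: "The sum of scores is then compared with a list of age-specific cut-off points standardized for Iranian children".

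**The concern.** A domain score is a short sum with fixed limits. A child with five items not yet achieved and one sometimes achieved scores 5. That is a legitimate answer pattern and a sign of severe delay. Distance from the mean cannot separate such a child from a data error, yet it is the only criterion the sentence supplies.

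Three consequences follow if the rule is applied to ASQ scores.

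- **Selection on the outcome.** Scores of randomised mothers' children would go missing because of their value, a few lines after the plan invokes ITT to deal with missing outcomes.
- **Asymmetry.** Where typical scores are high, the upper limit lies off the scale and only low scores can be lost.
- **Attenuation.** If levothyroxine works by reducing the number of severely delayed children, the rule removes the children who carry that effect, and more of them from the untreated arm.

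Grubbs' test also assumes normal data. The following paragraph of the same section provides for non-normal data with a rank test, so deletion is not needed to protect against extreme values.

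**Working it through.** **Inputs from the article.** Domain range 0–60 in steps of 5; threshold 4 SD; 183 mothers per arm in the SCH–TPOAb-negative trial (Table 2); 15% attrition. Children per arm: 183 × 0.85 = 155.6, taken as 156.

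**Not in the article.** Any ASQ mean or SD, the share of delayed children, their scores, and whether the mean and SD are taken per arm or pooled. These are assumptions below. The plan has no figure of its own on this point to reproduce.

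**Step 1: which scores can the rule reach?** A low score can be discarded only if mean − 4 SD > 0, that is SD < mean/4. A high score can be discarded only if mean + 4 SD < 60, that is SD < (60 − mean)/4. Deletion is therefore on the low side only when (60 − mean)/4 ≤ SD < mean/4.

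| Mean | Low side only when SD is from | to below |
|---|---|---|
| 40 | 5 | 10 |
| 45 | 3.75 | 11.25 |
| 50 | 2.5 | 12.5 |
| 55 | 1.25 | 13.75 |

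Example: at mean 50 and SD 10 the limits are 50 − 40 = 10 and 50 + 40 = 90. Scores below 10 go, and 90 cannot be reached. Outside the interval the picture changes. At mean 50 and SD 14 the lower limit is −6 and nothing can be deleted. At mean 40 and SD 4 the upper limit is 56, so high scores could go too.

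**Step 2: how much could be lost?** Illustration: 156 per arm, 4% delayed untreated and 2% treated, scores rounded to 5, arms pooled, one pass of the 4-SD rule, 2,000 simulated trials per setting. The expected number of delayed children is 156 × (0.04 + 0.02) = 9.4. The SD shown is that of the non-delayed children.

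| Non-delayed mean, SD | Delayed scores | Delayed children losing their score | Difference, all kept | Difference after rule |
|---|---|---|---|---|
| 50–55, 6–8 | 0–20 | about 37–74% | about 0.8–0.9 | about 0.2–0.5 |
| 50, 10 | 0–20 | about 17% | 0.81 | 0.65 |
| 50, 12 | 0–20 | about 4% | 0.73 | 0.69 |
| 50, 10 | 10–30 | about 1% | 0.61 | 0.60 |

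No high score was deleted in any setting. In the first row the pooled SD, delayed children included, was 9.0–10.0, inside the Step 1 interval.

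**Step 3: check by hand.** Before rounding and the ceiling, the true difference is (0.04 − 0.02) × (non-delayed mean − delayed mean). For delayed scores 0–20 this is 0.02 × (50 − 10) = 0.80 or 0.02 × (55 − 10) = 0.90; for 10–30 it is 0.02 × (50 − 20) = 0.60. In the worst setting (mean 55, SD 6) 74% are deleted. The survivors are the higher scorers, so their mean lies between 10 and 20. That leaves 0.02 × 0.26 × (35 to 45) = 0.18 to 0.23, which agrees with the simulated figure of about 0.2.

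**Step 4: a different model.** With 183 per arm, scores built from six simulated items and 6% versus 2% delayed, the 4-SD rule deleted 13–59% of delayed children. The difference fell from 0.95–1.78 to 0.65–1.00 points. Again every deleted score was low.

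**The case against.** **The sentence can be read narrowly.** It sits in a paragraph on dataset accuracy. If a value must be implausible on other grounds and also beyond 4 SD, in-range ASQ scores are untouched, and unbounded variables such as TSH or urinary iodine are the natural targets. That reading is possible, but the text gives no other test of implausibility and exempts nothing, so an analyst following it could discard ASQ scores.

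**ITT may not be broken.** What is discarded is a value, not a child, and the ITT sentence says it covers missing outcomes. This softens the conflict but does not remove the bias, because here the outcome's own value causes the missingness.

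**The practical loss may be small.** This stands. In the illustration with SD 6–8 the true difference is below one standard error (about 1.0–1.1 points), and power was about 11–13% before the discard and 6–8% after. The standardised effect is near 0.1, for which the article's own calculation asks for 2356 participants. With wider spread or milder delay, the rule does almost nothing. The illustration shows direction, not the loss of a detectable effect.

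**Stronger readings.** A reader might infer that the rule can delete only the lowest scorers, or that it removes the delayed children as a group. Neither follows without an ASQ mean and SD, and even where deletion is low-side only, just the most extreme children are reached. A reader might also infer that Grubbs' test, applied repeatedly, would strip out nearly all delayed children. The garbled sentence does not say that a Grubbs flag alone leads to discard, or that the test is repeated, so no size is given for it here.

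**Conclusion.** The point holds in a conditional form. As written, the rule covers the primary outcomes, needs no evidence of error, and can delete scores that the ASQ scale makes entirely possible. If scores sit towards the upper end with moderate SD, only very low scores are exposed, and any effect acting through fewer severely delayed children is biased towards zero.

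The size cannot be fixed from the article. Under the stated assumptions (156 per arm, 4% versus 2% delayed) it runs from about 1% of delayed children deleted (mean 50, SD 10, delayed scores 10–30) to about 74% (mean 55, SD 6, delayed scores 0–20). True differences of about 0.6–0.9 points become about 0.2–0.7. At larger SD, such as 14 at mean 50, the rule deletes nobody. At best, then, it does nothing for these outcomes; otherwise it deletes valid primary data.

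**What to change.** In the Statistical analysis section, exempt ASQ scores from the Grubbs and 4-SD discard, and state that:

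- ASQ data are corrected or excluded only if a domain score lies outside 0–60, an item is not scored 0, 5 or 10, or the entry is shown to be wrong against the completed questionnaire;
- every valid score of every randomised mother's child stays in the primary ITT analysis;
- outlier exclusion or a robust method is used for ASQ outcomes only as a sensitivity analysis.

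The planned histograms and cross-tabulations can stay as the means of finding entries to check. If the discard rule is kept for other variables, the sentence should say which ones, and whether a Grubbs flag alone is enough.

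The cost is a sentence or two of analysis wording, with no extra data or participants. It should be settled before the scores are analysed.

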## Results

Baseline characteristics of neonates according to their mothers’ thyroid status are presented in Table 2.

**Table 2 Tab2:** Baseline characteristics of neonates according to their mothers’ thyroid status

Characteristics	SCH-TPOAb^−^		SCH-TPOAb^+^		
	LT4 treatment (*n* = 183)	Placebo (*n* = 183)	LT4 treatment (*n* = 65)	Placebo (*n* = 66)	Euthyroid TPOAb^−^ (*n* = 1028)
Gestational age, mean (SD)	38.03 (1.4)	37.9 (1.5)	39.3 (1.3)	38.4 (1.7)	39.4 (1.4)
Birth weight, mean (SD)	3190.82 (455.13)	3203.1 (497.1)	3139.1 (287.6)	3127.7 (523.5)	3236.6 (448.8)
Birth height, mean (SD)	50.1 (2.3)	50.2 (2.7)	49.5 (1.7)	50.3 (1.5)	50.1 (2.3)
Birth head circumference, mean (SD)	34.6 (1.4)	34.7 (1.6)	34.5(1.1)	34.9 (1.4)	34.7 (2.3)
TSH (μIU/mL), Median (IQ)	1.1 (0.5–2.1)	1.1 (0.5–1.9)	1.3 (0.45–1.9)	1.0 (.43–1.9)	0.90 (0.4–1.7)

*SCH* subclinical hypothyroidism, *TPOAb* thyroid peroxidase antibodies, *TSH* thyroid-stimulating hormone, *LT4* levothyroxine

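### Comparisons with the much larger euthyroid group should not assume equal variances: use robust standard errors in the primary GLM, and Welch's t in place of Student's t (minor)

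*Protocol article*

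**What the plan says.** The protocol article's Power calculation section sets the scope: "The purpose of this study will be multiple comparisons of five groups". The five are treated and untreated TPOAb+, treated and untreated SCH-TPOAb−, and healthy (euthyroid) controls. Table 2 in Results gives the sizes: 65 and 66, 183 and 183, and 1028.

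For continuous variables, the Statistical analysis section first tests normality; "in case of rejection, the Mann–Whitney non-parametric U test will be applied", and "otherwise independent Student’s t test will be used to find the differences". Equality of variances is not mentioned.

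The same section then states: "The primary analysis for the study is to assess the effect of treatment on the aspects of psychomotor developmental status". It continues: "Therefore generalized linear models (GLM) will be conducted modeling the variables". Crude and adjusted models follow. The family, the variance estimator, and whether all five groups enter one model are not stated.

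**The concern.** Student's t conventionally uses one pooled SD. At about 16:1 that pooled SD is almost entirely the euthyroid SD, while most of the sampling error in the difference comes from the small group. If the small group is more variable than the euthyroid children, the standard error is too small and false differences become too frequent. If it is less variable, the standard error is too large and power is lost. A normality check does not detect either case.

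A common-variance Gaussian model over all five groups works the same way, and there one residual variance would also set the intervals for the two levothyroxine contrasts. At stake are the comparisons with euthyroid children, which the Discussion counts as part of the study's key strength and, depending on how the GLM is fitted, the treatment contrasts.

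**Working it through.** **Inputs.** Group sizes are from Table 2 (for example "LT4 treatment (*n* = 65"). Attrition is from the Power calculation section: "We will consider q = 15% attrition as well". Applying 0.85 gives 65 → 55, 183 → 156 and 1028 → 874. The ratio r of small-group SD to euthyroid SD is an assumption shown over a range, because no ASQ SD is given.

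**The plan's own figure.** The sample-size list works "with power of 80% and type one error of 5" per cent. With g = 5 the printed formula at d = 0.4 gives 3 × (1.960 + 0.842)² / 0.16 + 3.84 × 2 / 5 = 147.2 + 1.5 = 148.7, against 149 in the text. The other eight values agree to within one participant. The formula takes a single standardised d and does not address unequal SDs, so the plan has no figure to reproduce on this point.

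**Student's t under unequal SDs.** Put the euthyroid SD at 1.

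- Pooled SE = √{[(n₁−1)r² + (n₂−1)] / (n₁+n₂−2) × (1/n₁ + 1/n₂)}
- Correct SE = √(r²/n₁ + 1/n₂)
- True type I error ≈ 2{1 − Φ(t_crit × pooled SE / correct SE)}

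Example with 55 vs 874 and r = 1.17: pooled variance = (54 × 1.369 + 873) / 927 = 1.021. Pooled SE = √(1.021 × 0.01933) = 0.1405. Correct SE = √(1.369/55 + 1/874) = 0.1613. Their ratio is 0.871, so the error is 2{1 − Φ(1.9625 × 0.871)} = 8.7%; simulation gives 8.9%.

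| r | pooled SE / correct SE | Student's t, formula | Student's t, simulation |
|---|---|---|---|
| 0.64 | 1.47 | 0.4% | 0.4% |
| 0.80 | 1.22 | 1.7% | 1.8–1.9% |
| 0.95 | 1.05 | 4.0% | – |
| 1.05 | 0.96 | 6.0% | – |
| 1.17 | 0.87 | 8.7% | 8.9% |
| 1.30 | 0.79 | 11.9% | 11.8% |

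Welch's t stays at about 5% throughout (4.8% to 5.2% in simulation). At full numbers, 66 vs 1028, the results are essentially the same. At 183 vs 1028 the distortion is smaller: 7.9% at r = 1.17.

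**Randomised pairs, two-sample t.** For 65 vs 66, simulated error is 4.9% to 5.1% for r from 0.64 to 1.5. For 183 vs 183, pooled and correct SE coincide at every r.

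**Is equal spread a safe default?** Table 2 gives four neonatal measures with SDs. The 16 ratios to euthyroid run from 1.1/2.3 = 0.48 (head circumference, TPOAb+ treated) to 1.7/1.4 = 1.21 (gestational age, TPOAb+ untreated). Birth weight gives 287.6/448.8 = 0.64 and 523.5/448.8 = 1.17 in the two TPOAb+ arms.

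**If one residual variance is fitted to all five groups.** Residual SD s = √{Σ(nᵢ−1)sᵢ² / (1525 − 5)}.

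- With Table 2 gestational-age SDs, s = 1.42. For untreated TPOAb+ vs euthyroid the model SE is 1.42 × √(1/66 + 1/1028) = 0.181, against a correct 0.214: ratio 0.85.
- With head-circumference SDs, s = 2.06. For treated TPOAb+ vs euthyroid the SEs are 0.264 and 0.154: ratio 1.71.
- For the TPOAb+ levothyroxine contrast on head circumference, the SEs are 2.06 × √(1/65 + 1/66) = 0.360 and √(1.1²/65 + 1.4²/66) = 0.220: ratio 1.64, a true error of about 0.1%.
- If all four non-euthyroid groups had SDs 1.2 or 1.3 times the euthyroid SD, s would be 1.069 or 1.106. The SE ratio for a levothyroxine contrast would be 1.069/1.2 = 0.89 or 1.106/1.3 = 0.85, with errors of about 8.1% or 9.5%.

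**The case against.** Four points can be made for the plan.

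1. *Student's t will rarely be reached for the ASQ domains.* Each is six items scored 10, 5 or 0, so it moves in 5-point steps and is capped at 60. In simulations with assumed means of 30 to 52 and SDs of 8 to 10, Shapiro–Wilk rejected every time at n = 874 and n = 155. This stands: swapping the t test alone would seldom change a primary result. It is not a full rescue, because Mann–Whitney is also sensitive to unequal spread, though less so: 1.1% at r = 0.64, 6.6% at 1.17 and 8.3% at 1.30 for 66 vs 1028.

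2. *The GLM is primary, and its variance estimator may be settled in a fuller document.* This stands as far as it goes: that silence is not an error, and the five-group common-variance fit is a possibility, not the plan's text.

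3. *The randomised comparisons are 1:1.* This stands for separate two-sample t tests. A reader might infer that the levothyroxine comparison is invalid as planned. The document does not support that; it would be affected only through a pooled five-group model.

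4. *Table 2 is not ASQ data.* This stands. A reader might infer that ASQ spread is known to differ, or that a group with more delayed children must have a larger SD. The document gives no ASQ SD, only one of the 16 ratios reaches 1.2, and eight are below 1. Nor does just any SD difference make the results wrong, since a 5% difference gives 4.0% or 6.0%.

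**Conclusion.** The point holds as a minor one. The plan names a pooled-variance test, conditional only on normality, for a set of comparisons that includes 16:1 and 5.6:1 group sizes. Under a material SD difference, tests and intervals against the euthyroid group are miscalibrated in either direction: roughly 0.4% to 12% instead of 5% over SD ratios of 0.64 to 1.3. These figures assume normal data and 15% attrition in every group. The size for the real outcomes is unknown; Table 2 shows only that equal spread should not be taken for granted in these children. Because ASQ scores will probably fail the normality check, the primary GLM is where the change matters most, and that part is conditional on a common-variance fit across all five groups.

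**What to change.** In the Statistical analysis section, state that the primary GLM is reported with heteroscedasticity-robust (HC3) standard errors, or with group-specific residual variances, for every contrast among the five groups. Use Welch's t wherever the section would use Student's t.

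The cost is one line of wording and no extra data. If variances are in fact equal, simulated power at d = 0.4 with 55 vs 874 children falls from 82.2% with Student's t to 81.2% with Welch's.

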The key strength of the present study is assessing the neurodevelopmental status of the offspring of both groups of TPOAb^+^ cases and SCH-TPOAb^−^ women along with euthyroid TPOAb^−^ women, considering their iodine sufficiency status during pregnancy. We are not aware of any other studies that have considered all these components simultaneously. The other strength of this study is the ASQ and the number of characteristics assessed. First,the Persian version of the ASQ has appropriate validity and reliability for screening developmental disorders in Iran [26]. It has also been proven to be a valid and/or reliable screening test, i.e. it has translated and culturally adapted versions in several studies in different populations of children [28]. In a multinational trial involving 18 countries in Asia, Africa, Europe, North America, and South America reported in 2007, the sensitivity and specificity were determined to be 88% and 82.5%, respectively [45, 46]. It also uses simple and straightforward language; simple illustrations are provided for many items adding to their clarity of meaning, which makes it a feasible and easy-to-use test [47]. It is inexpensive [47, 48] and takes about 10 min to administer [47]. Administration does not require specialized training. This series of developmental screening questionnaires includes five developmental domains: gross motor skills; fine motor skills; communication; problem-solving; and personal–social domains. The questionnaires cover 19 age groups in the range of 4–60 months [49].

The main challenge of this study will be the rate of attrition; however, its pilot study received a response rate of > 80%. The other challenge of this study is lack of awareness of other factors that may influence the developmental status of the children, e.g. nutritional inadequacies [50], although the randomized allocation of study participants minimizes this effect.

By conducting this study, we hope to better understand the beneficiary impact of treatment of mild forms of thyroid dysfunctions during pregnancy, considering the influential effect of iodine status. This piece of knowledge has the potential for evidence-based decision-making regarding the universal screening for thyroid dysfunction and/or thyroid autoimmunity.

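### Interaction and subgroup tests over an open list of covariates share the plan's only significance rule, p < 0.05, so the chance of a false effect modification is far above 5%

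*Protocol article*

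**What the plan says.** All the relevant rules are in the Statistical analysis section of the protocol article.

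- **Primary analysis.** This is the effect of treatment on the developmental domains, by generalised linear models.
- **Interactions and subgroups.** Interaction terms between treatment and some other covariates are then to be added, and "a subgroup analysis will be run to check the effect of treatment on the levels of covariates, variables such as parity, socioeconomic status". The sentence goes on to type of delivery, lactic status and urinary iodine, and ends with *and so on*. Five modifiers are named and the number is not fixed.
- **A second provision.** Earlier in the section: "Subgroup analysis for important confounding variables will be run, if needed".
- **Decision rule.** The section closes with one threshold, p < "0.05 is considered statistically significant". No other rule is given for any analysis.

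The Power calculation section makes all five ASQ domains primary outcomes and states that "The purpose of this study will be multiple comparisons of five groups". The Overall trial design section describes two randomised trials, one in TPOAb-positive women (n = 131) and one in SCH–TPOAb-negative women (n = 366).

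The Discussion criticises earlier trials for not considering iodine deficiency. It then says "we hope to better understand the beneficiary impact of treatment of mild forms of thyroid dysfunctions during pregnancy, considering the influential effect of iodine status", followed by "This piece of knowledge has the potential for evidence-based decision-making regarding the universal screening".

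**The concern.** As written, a test of whether levothyroxine works differently by parity or mode of delivery is judged by the same rule as the primary test of whether it works at all. With five named modifiers, five domains and possibly two trials, many tests are each run at 5%. Because the list is open, nobody could later say how many were tried. A chance interaction would meet the plan's only criterion for significance.

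This family is distinct from the multiplicity of the main comparison. Adjusting the primary analysis over domains or groups would leave every interaction test at an unadjusted 5%.

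At stake is how far any reported subgroup effect can be trusted. A spurious finding, such as apparent benefit confined to one iodine or parity level, could be cited in the screening debate to which the Discussion refers. A genuine iodine interaction would also suffer. Iodine is only the last of five examples in the analysis section, so a real result there could not be told apart from one picked out of many.

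**Working it through.** The document states no error rate for these tests, so there is no figure of its own to reproduce. The rate is derived as follows.

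**Inputs from the document**
- Level per test: 0.05, taken as two-sided (Statistical analysis; the sample-size formula also uses z at 1 − α/2).
- Named modifiers: 5 (Statistical analysis).
- Primary domains: 5 (Power calculation).
- Randomised trials: 2 (Overall trial design).

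**Assumptions, not in the document**
- No true interaction.
- One interaction test per modifier and domain, either once (one trial or one pooled model) or once in each trial.
- Correlation between test statistics across domains 0.3–0.7, with 0.9 as an extreme. Correlation across modifiers 0–0.5. The two trials are independent.

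**Step 1: number of tests**
- One analysis: 5 × 5 = 25 tests; expected false positives 25 × 0.05 = 1.25.
- Two trials analysed separately: 50 tests; expected false positives 50 × 0.05 = 2.5.

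**Step 2: independent tests**, P(at least one) = 1 − 0.95^k
- k = 5 (five modifiers, one domain): 22.6%
- k = 13: 48.7%; k = 14: 51.2%
- k = 25: 72.3%
- k = 50: 92.3%

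**Step 3: correlated tests**, by simulation of null z-statistics (200,000 draws per setting) for 5 modifiers × 5 domains. For separate trials, P₂ = 1 − (1 − P₁)².

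| Domain correlation | Modifier correlation | One trial or pooled | Two trials |
|---|---|---|---|
| 0.3 | 0 | 69% | 90% |
| 0.5 | 0 | 64% | 87% |
| 0.7 | 0 | 55% | 80% |
| 0.7 | 0.5 | 46% | 71% |
| 0.9 | 0 | 41% | 66% |
| 0.9 | 0.5 | 34% | 56% |

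Over the main range (domain 0.3–0.7, modifier 0–0.5) this is 46–69% for one analysis and 71–90% for two. The lower end, 46%, is about nine times 5%.

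**Step 4: fewer modifiers** (domain correlation 0.5, independent modifiers)
- Three modifiers (parity, socioeconomic status, urinary iodine): about 46% for one analysis, 70% for two.
- One modifier over five domains: 18% for one analysis, 33% for two.

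**Step 5: effect of adjustment**
- One pre-named modifier over five domains with each test at 0.05/5 = 0.01: 1 − 0.99⁵ = 4.9%.
- The same modifier in two separate trials with each test at 0.05/10 = 0.005: 1 − 0.995¹⁰ = 4.9%.
- Holm's procedure starts from these thresholds and keeps the familywise error at or below 5%.

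**The case against.** **This is a condensed article, and a separate analysis plan may fix the list.** A missing exploratory label or a missing ranking of modifiers would not be a finding by itself. What stands is narrower: the text positively commits to interaction and within-level analyses over an open list, and gives one threshold for everything. That is a rule fixed badly, not just a detail left for later.

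**The text already has a hierarchy.** It names a primary analysis and brings in interactions afterwards, and the threshold sits in the sentence on software. This is fair as far as it goes. But no consequence follows from the order, since the same p < 0.05 governs both.

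**The test count is assumed.** The article does not say that every modifier is tested in every domain, nor whether the two trials are modelled separately or within the five-group comparison. This stands, and it limits the figures. A reader might infer that a false subgroup effect is simply more likely than not. The documents do not support that: for one trial or a pooled analysis the probability drops below 50% at high correlation, and for a single domain it is 22.6%. The figure of 87% likewise holds only if the trials are analysed separately.

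**The Discussion promises no subgroup claim.** Correct. A reader might take its remarks on iodine and screening as a commitment to act on a subgroup result. The text expresses only a hope and a potential, and considering iodine status could mean adjustment for it.

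**The sentence on subgroups for confounders may not mean effect modification at all.** Also fair. It is ambiguous, and no test from it is counted above.

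**Conclusion.** The point holds as a defect in a stated rule and should be corrected. Under the assumptions given, the chance of at least one false-positive interaction is about 46–69% for one trial or one pooled analysis (34–41% at domain correlation 0.9) and about 71–90% if the two trials are analysed separately. The correlations are assumed because the document gives none. Every case is well above 5%, and none counts covariates beyond the five named or tests within covariate levels, both of which the text allows.

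The primary treatment comparison is not affected. Nor do the documents establish that iodine must be the single lead modifier: the Discussion stresses it, but the analysis section does not rank it.

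**What to change.** In the Statistical analysis section:

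1. Replace the open list with a closed one, deleting *and so on* and *if needed*.
2. State that effect modification is judged by the treatment-by-covariate interaction test and not by tests within covariate levels.
3. State that all interaction and subgroup analyses are exploratory, reported as estimates with 95% confidence intervals together with the number examined, and that no significance claim is made from them.
4. If the sponsor wants one confirmatory modifier, exempt it from item 3 by naming it in advance. Holm-adjust its interaction test over the five domains, and over the two trials as well if they are analysed separately. Urinary iodine from the first-visit samples is the natural choice given the Discussion, but the choice is the sponsor's.

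This takes a few sentences and no new data. The Trial status section gives recruitment as ongoing and primary completion as February 2019, so on the document's own dates the change could precede the analysis. The price is that nominally significant subgroup results become hypothesis-generating only, and an adjusted lead test is less sensitive than an unadjusted 5% test.
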